## Abstract

**Background:**

To evaluate the effectiveness of a new multifactorial intervention to improve health care for chronic ischemic heart disease patients in primary care. The strategy has two components: a) organizational for the patient/professional relationship and b) training for professionals.

**Methods/design:**

Experimental study. Randomized clinical trial. Follow-up period: one year. Study setting: primary care, multicenter (15 health centers). For the intervention group 15 health centers are selected from those participating in ESCARVAL study. Once the center agreed to participate patients are randomly selected from the total amount of patients with ischemic heart disease registered in the electronic health records. For the control group a random sample of patients with ischemic heart disease is selected from all 72 health centers electronic records.

Intervention components: a) Organizational intervention on the patient/professional relationship. Centered on the Chronic Care Model, the Stanford Expert Patient Program and the Kaiser Permanente model: Teamwork, informed and active patient, decision making shared with the patient, recommendations based on clinical guidelines, single electronic medical history per patient that allows the use of indicators for risk monitoring and stratification. b) Formative strategy for professionals: 4 face-to-face training workshops (one every 3 months), monthly update clinical sessions, online tutorial by a cardiologist, availability through the intranet of the action protocol and related documents.

Measurements: Blood pressure, blood glucose, HbA1c, lipid profile and smoking. Frequent health care visits. Number of hospitalizations related to vascular disease. Therapeutic compliance. Drug use.

**Discussion:**

This study aims to evaluate the efficacy of a multifactorial intervention strategy involving patients with ischemic heart disease for the improvement of the degree of control of the cardiovascular risk factors and of the quality of life, number of visits, and number of hospitalizations.

**Trial registration:**

NCT01826929

## Background

The medical, health care, financial, personal and family burden of chronic disease is one of the main threats to the sustainability of the health system. At present, 70% of health care expenditure is used to treat chronic diseases [1]. Accordingly, health care systems are now moving towards more patient-centered models based on self-care and therapeutic education as ways of promoting the participation of the patients in their own treatment [2].

Cardiovascular disease (CVD) is one of the main chronic diseases, and is in fact the leading cause of death in the Spanish population. In 2007 it accounted for 124,126 deaths in Spain, representing 32% of all deaths [3]. In Spain, ischemic heart disease (IHD) causes most CVD deaths (30% overall; 37% in men and 24% in women). The hospital morbidity rate for IHD was 317 per 100,000 inhabitants (447 in men and 189 in women) [3]–[5].

Lifestyle changes (giving up smoking, a Mediterranean diet and exercise) have been shown to decrease cardiovascular morbidity and mortality in patients with IHD. In addition, much evidence now exists concerning pharmacological treatment aimed at the associated risk factors [5].

The latest European guidelines aim to increase the involvement of the primary care professionals in the implementation of the preventive activities for these patients. The guidelines emphasize a patient-centered approach, joint decision-making, and the importance of establishing realistic and feasible objectives, as tools to improve compliance with medication and lifestyle changes [6]–[8]. A recent Cochrane library review stresses the importance of primary care and the need to improve the organization of the health care services for the secondary prevention of IHD [9].

However, difficulties exist when incorporating the results of the various studies into clinical practice. Comparison of the results from the EUROASPIRE I to the EUROASPIRE III studies, in patients with IHD, shows that the prevalence of risk factors remains high: smoking hardly changed (20.3%, 21.2%, and 18.2%), obesity (body mass index ≤ 30) increased from 25% to 32.6% and 38%, and poorly controlled blood pressure (BP) (≥ 140/90 mmHg) changed very little (58.1%, 58.3%, and 60.9%). Only in the prevalence of hypercholesterolemia was an important decrease observed, from 94.5% to 76.7% and 46.2%. Concerning the use of drugs, between the EUROASPIRE I and the EUROASPIRE III studies [10] antiplatelet drugs rose from 80.8% to 93.2%, beta blockers from 56% to 85.5%, antihypertensive drugs from 84.5% to 96.8%, and lipid-lowering drugs from 32.2% to 88.8%. Although improvements have been noted, an important percentage of patients still exists in whom the control of risk factors could be improved.

Studies carried out in our area show that 54% of the patients with a history of myocardial infarction had hypercholesterolemia, 41% had high blood pressure, 11% were smokers, and 19% were obese; in addition, there was a clear underuse of medication [11].

Therapeutic educational interventions, such as the Chronic Care Model (CCM) that includes educational, organizational and community participation interventions; the Stanford Expert Patient Program (EPP); and the Kaiser Permanente model [12,13] have all shown their benefit in patients with a high CVD risk and their effect on clinical measures and health care use.

Based on these models, various initiatives to improve the secondary prevention of coronary disease patients have been undertaken in our area [14,15]. The ICAR study assessed the efficacy of an intensive secondary prevention program of coronary disease carried out in primary care. However, improvement was only found in blood pressure control and an increase in HDL-cholesterol concentrations [14]. The PREseAP study assessed the efficacy of an intervention carried out by nurses, but with no positive results [16,17]. Another intervention study also from primary care [18] found that admissions to hospital were significantly reduced, but no other clinical benefits were shown, possibly because of a ceiling effect related to improved management of the disease. Given these poor results, we designed a multifactorial intervention based on the CCM, integrating professionals from cardiology services and primary care, in an attempt to improve the degree of control of CVRF and reduce the number of hospital admissions.

### Main objective

To evaluate the effectiveness of a new multifactorial intervention in order to improve health care for chronic IHD patients in primary care. The strategy consisted of two components: a) organizational for the patient/professional relationship, and b) formative for the professionals.

### Specific objectives

Level of control/follow-up of the following variables: blood pressure, capillary blood glucose, HbA1c, LDL cholesterol, body mass index, therapeutic compliance, exercise, smoking, adherence to a Mediterranean diet, incidence of hospital admissions related to vascular disease, annual primary care visits (number of visits in one year) and drug use (antiplateled drugs, beta blockers, ACE inhibitors/ARA II, statins).

### Hypothesis

A multifactorial primary care intervention based on chronic models [12] can improve the level of control and reduce the number of hospital admissions in patients with IHD.

## Methods/design

### Study design

Experimental design. Type of study: open randomized clinical trial. Follow-up period: one year.

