### Randomization, allocation and implementation

Valencia is a Mediterranean Spanish Region with 5 million inhabitants. In 2007, 800 primary care physicians and nurses started the ESCARVAL primary prevention cohort study [20]. 72 Health centers (HC) participated including 50000 patients.

For the intervention group in the PROPRESE study 15 HC are selected from those participating in ESCARVAL. Once the center agreed to participate patients are randomly selected from the total amount of patients with IHD registered in the electronic health records.

For the control group a random sample of patients with IHD is selected from all 72 HC electronic records.

Patients are enrolled by their primary care physicians who will offer to participate to the randomly selected patient.

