## Discussion

IHD is one of the main causes of death despite the great capacity for prevention that is available. Nowadays, multiple therapeutic tools of proven efficacy exist to control the main CVRF, as well as guidelines and protocols endorsed by the main scientific societies [5]–[7,19].

However, the degree of control of the CVRF in patients with IHD is low [15]–[17], which results in a higher use of health services. The frequency of primary care visits of a person with diabetes in Spain is 28 per year, even though this does not necessarily imply greater control [21]. Two of the main reasons for this are lack of treatment compliance and therapeutic inertia in the office, control of which has not improved in recent years [22]–[25].

The CCM [12] consider acting on these factors through new approaches. These models involve patient training to achieve greater autonomy and information, and the identification of high-risk patients to give them a more individualized and protocolized care.

Accordingly, the present study involved an organizational intervention based on CCM together with an educational intervention, integrating cardiology service professionals and primary care professionals (general practitioners and nurses), in an attempt to improve the degree of control of CVRF and decrease the number of hospitalizations.

This intervention aims to increase the degree of self-control for these patients as well as their ability for self-care and decision making to improve their long-term survival. At the same time, the greater degree of information and education can facilitate the increase in compliance that should result in an improvement in the therapeutic objectives.

The health care team-work methodology will be modified with more resolute and specific patient-centered office visits, without increasing the work load in the primary care offices. This is aimed at reducing clinical inertia.

The Abucasis computer system, available in secondary and primary care offices, facilitates the interaction between levels of health care as well as being a common and unique site for the patient to record and control the main CVRF.

The validity of the results, which depends on the representativeness of the sample, is controlled by the selection criteria designed and in relation to study power, through the sample size calculated taking into account any unexpected loss by controlling the random error.

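### The article calls the study a randomized clinical trial, but it describes random sampling of two groups from different sources, not random allocation to arms

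*Protocol article*

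**What the plan says.** The design label appears twice. The abstract gives "Experimental study. Randomized clinical trial. Follow-up period: one year", and the Study design section gives "Type of study: open randomized clinical trial".

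The section headed Randomization, allocation and implementation then describes how the groups are formed:

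- Centers, intervention group: "For the intervention group in the PROPRESE study 15 HC are selected from those participating in ESCARVAL". No random mechanism is given for this choice.
- Patients, intervention group: "Once the center agreed to participate patients are randomly selected from the total amount of patients with IHD registered in the electronic health records". Their own physicians then invite them.
- Control group: "For the control group a random sample of patients with IHD is selected from all 72 HC electronic records".

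Table 4 repeats the scheme with 350 patients per group. The Blinding section adds that controls are picked only after the intervention, although they cover the same period. The Statistical analysis section lists chi-square, t test and ANOVA, and says that a multivariate analysis will evaluate the intervention effect.

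**The concern.** Random sampling and random allocation do different work. Sampling at random from a register supports generalizing to that register. Allocating at random between arms makes the arms comparable apart from chance. The article describes the first and takes the label of the second.

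If the label stands, readers and evidence reviews will assume that measured and unmeasured differences between the groups are balanced apart from chance. Nothing in the described procedure provides that. Centers that were chosen and agreed to join an improvement programme may differ from the register as a whole in prior admissions, risk-factor control or completeness of recording. A larger sample would make the comparison more precise without removing such a difference.

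**Working it through.** This is mainly a comparison of statements, in four steps.

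**1. What decides the arm?**

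- *Center level.* Fifteen of the 72 ESCARVAL centers enter the intervention (15/72 = 20.8%). They are selected and must agree. No sequence or random draw between intervention and control is described for centers.
- *Patient level, intervention.* The random draw takes place inside centers that are already committed to the intervention. Everyone drawn belongs to the intervention group, so the draw settles inclusion and not arm.
- *Patient level, control.* A second, separate draw is made from the 72-center register. Everyone drawn is a control.

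At no step could the same center or patient have been assigned to either arm by one random process. Arm follows from which source a patient was drawn from.

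**2. When is each group formed?** Random allocation needs a common point at which units are still unassigned. The Blinding section places control selection after the intervention, when the intervention group already exists. That rules out joint allocation and also gives the groups different times and routes of entry.

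**3. Do the relevant sections agree with one another?** The abstract's own description of group formation, the allocation section, the Blinding section and Table 4 are consistent. Only the label, in the abstract and under Study design, conflicts with them.

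**4. Are the two sources separate?** They are not stated to be. Controls come from all 72 centers and the 15 are not excluded. Patients of professionals trained under the programme can therefore be sampled as controls. The article does not give the number of ischemic heart disease patients per center, so the expected overlap needs an assumption:

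expected controls from intervention centers = 350 × share of eligible patients held by the 15 centers

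- equal center size (share 15/72): 350 × 0.208 = 73
- share 10%: 350 × 0.10 = 35
- share 30%: 350 × 0.30 = 105

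These figures show possible contamination. They do not measure the confounding in steps 1 and 2, for which the article contains no usable number.

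**The case against.** The best defence is that the article does not rely on simple tests alone. It assigns the intervention effect to a multivariate analysis, whose covariates may be set out in a full protocol or analysis plan that is not shown. Hospitalizations are measured at the beginning and end of the study, Table 4 lists baseline data, and the data come from the electronic record, so the material for adjustment is largely planned. This stands, and the lack of a covariate list is not part of the point. But adjustment, however well specified, does not make the study randomized.

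The flow diagram is also not shown. The allocation section and Table 4 are explicit, however, and no visible text mentions a sequence, assignment or concealment.

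Several stronger readings are tempting but not supported:

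- *The causal claim is wrong.* A reader might infer this from the mislabelling. The text supports only that the claim is not backed by randomization; adjusted effects can be estimated in non-randomized controlled studies.
- *Unadjusted tests will credit baseline differences to the intervention.* The planned multivariate analysis contradicts this.
- *Consent separates the arms.* The Participants and Informed consent sections require consent from all patients, so as written it does not.
- *The centers volunteered.* The article says that they were selected and agreed, without giving the selection rule.
- *The article claims that representativeness makes the arms comparable.* The Discussion says "The validity of the results, which depends on the representativeness of the sample, is controlled by the selection criteria", but the sentence goes on to power and sample size. It is a loose remark on sampling and precision.
- *A bias in mmHg.* One could assume a 2 to 3 mmHg baseline difference and call it 40 to 60% of the 5 mmHg in the sample size section (2/5 and 3/5). No source in the article supports the assumption, and the primary outcome is hospitalizations.

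**Conclusion.** The design label is wrong as written. The procedure is a non-randomized controlled comparison in which patients are randomly sampled within each source. Arm is confounded with center selection and agreement, and with route and time of entry. The error matters because the label sits in the abstract and methods and governs how every result will be read.

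Neither the direction nor the size of any bias in hospitalizations can be determined from the article. The conclusion rests on taking the allocation section, Blinding section and Table 4 at face value, and on the unseen flow diagram not describing a random assignment that all of them omit.

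**What to change.** 1. Replace the randomized label with *non-randomized controlled study* in the abstract and under Study design. Retitle the allocation section as sampling and group selection.
2. Make a baseline-adjusted comparison the primary estimate: hospitalizations in the study year, intervention versus control patients, adjusted for prior-year hospitalizations and for baseline characteristics in the electronic record (for example age, sex and diabetes).
3. Draw control patients from the ESCARVAL centers other than the 15 intervention centers (72 − 15 = 57).
4. State in the conclusions that the estimate rests on adjustment for measured confounders and not on randomization.

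The cost is a weaker but correct label, some wording, and a modest extra extraction from a record already in use. Step 3 removes the overlap but leaves no center contributing to both groups, so unmeasured center differences remain and step 4 is needed. Randomizing the agreeing centers would be a new design and is not part of this correction.

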### Participants

Setting: Primary Health Care. Valencian Community (Spain).

15 Health centers: Alicante-Cabo-Huertas, Alicante-Campello, Alicante-Plà Hospital, Castellón-Dolores-Cano-Royo-Villareal, Castellón-La-Bobila-Villareal, Castellón-Cariñena-Villareal, Castellón-Nules, Castellón-Vall d’Uxo I and II; Valencia-S Pau, Valencia-R-Argentina, Valencia-Benimaclet and Valencia-Serreria-II.

Inclusion criteria: patients with a diagnosis of IHD of any site (ICD-10 codes from 410 to 414 inclusive); age from 30 to 80 years; signed written informed consent. Exclusion criteria: lack of consent; immobilized patients; patients with serious health problems or with a low life expectancy.

Data are collected from electronic health record system.

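### The IHD criterion pairs an ICD-10 label with ICD-9 codes and sets no diagnosis date, so a control first coded during follow-up could qualify through a counted admission

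*Protocol article*

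**What the plan says.** All references are to the protocol article.

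- **Participants** gives the inclusion criteria as "patients with a diagnosis of IHD of any site (ICD-10 codes from 410 to 414 inclusive); age from 30 to 80 years", plus signed consent. The exclusions are: "Exclusion criteria: lack of consent; immobilized patients; patients with serious health problems or with a low life expectancy". None concerns an acute or recent event, and no date is attached to the diagnosis. The section adds that data come from the electronic health record.
- **Randomization, allocation and implementation** describes two draws. Intervention patients are sampled from the registered IHD patients of 15 centers once each center has agreed to take part. For the other arm: "For the control group a random sample of patients with IHD is selected from all 72 HC electronic records".
- **Blinding** says that controls are picked once the intervention has been delivered, but for the same span of time.
- **Outcome measures** names the number of hospitalizations, by cause, as the primary outcome, measured at the beginning and end of the study.
- **Main objective** speaks of an intervention "to improve health care for chronic IHD patients in primary care". **Hypothesis** says that it "can improve the level of control and reduce the number of hospital admissions in patients with IHD", without the word chronic.

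**The concern.** The code range decides who can be sampled in both arms, because both are drawn from coded records. As printed it names a code system and a set of codes that do not belong together, so whoever runs an extraction must decide which half to believe. There are two draws, at different times and from different sets of centers, and nothing printed ensures that both settle the question in the same way.

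The second issue is when the code was entered. Read as ICD-9, the range covers acute infarction (410) and other acute or subacute forms (411). With no date rule, a person becomes eligible on the day such a code is entered. For an arm selected at the start of follow-up this does little harm, since the code must already be there. For an arm selected after the follow-up period, the event that makes a person eligible can lie inside the window over which the primary outcome is counted. Eligibility and outcome could then be the same event, in the control arm only.

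**Working it through.** The article gives no figure for this point, so there is none to reproduce. The check sets the passages side by side and adds one piece of arithmetic.

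**Step 1: label against codes.** ICD-10 codes begin with a letter, and its ischemic heart disease block is I20-I25. Three-digit numbers from 410 to 414 are the corresponding ICD-9 block. This is a basic property of the two classifications; the article prints no code list.

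| System used by the records | Effect of the printed criterion |
|---|---|
| ICD-9 | The range returns the IHD block; only the label is wrong |
| ICD-10 | The range matches nothing; the failure is seen at once and the query must be rewritten |

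The article does not say which row applies. In either case the intended condition is clear in words: IHD of any site.

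**Step 2: timing of each draw against the outcome window.**

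| | Intervention arm | Control arm |
|---|---|---|
| Source of patients | 15 centers | 72 centers |
| When selected | After the center agrees, before the first visit | After the intervention is delivered |
| Window for hospitalizations | One year of follow-up | Same period |
| Must the IHD code precede the window? | Yes, in effect: the patient is found by it before follow-up starts | No: the code need only exist when the draw is made |

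The asymmetry follows from the last row. A person free of recorded IHD at the start, admitted with a first infarction during the year and coded then, cannot be drawn into the intervention arm at its start. The same person can be drawn as a control. The infarction admission then lies inside the counted year.

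**Step 3: what one such control contributes.** By construction that control carries at least one admission. Table 4 plans 350 controls. One such patient adds 1/350 = 0.0029 admissions per control patient. In general, if a fraction *p* of controls enters this way, the control mean rises by at least *p* through the qualifying admissions alone. Under this mechanism the intervention arm gains nothing comparable, so any effect would favor the intervention. The article gives neither *p* nor an expected admission rate, so the shift cannot be put as a share of the outcome.

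**Step 4: does another rule close the gap?** The exclusions do not address recent events. The Randomization section says in general that primary care physicians enroll patients. Table 4 lists that step, with the eligibility criteria, under the intervention group; its control entry is only a random sample of 350 from the records. Even where physicians apply the criteria to controls, a patient first coded during the year meets them as written.

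**The case against.** The strongest reply is that this is a labelling slip. The condition is stated in words, 410-414 is the whole ICD-9 IHD block, and the natural ICD-10 counterpart is the same disease block. Both arms come from centers in one network, and nothing indicates that different lists were used. That stands: the mislabel alone does not show that the wrong patients were drawn.

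Four stronger readings are tempting, and the article does not support them.

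- A reader might infer that the extraction would yield nobody. That holds only for a literal query on ICD-10 fields, which could not pass unnoticed.
- A reader might infer that this is the sole objective criterion. Age from 30 to 80 years stands in the same sentence, and signed consent can be verified.
- A reader might infer that acute codes contradict an objective about chronic IHD. An acute code in a primary care record may mark a past infarction in a patient now in long-term follow-up, and the hypothesis refers simply to patients with IHD. Chronic is left undefined, not contradicted.
- A reader might assume a share of recent acute cases and a raised admission rate, and so compute a share of admissions. Such inputs have no source in the article, and a share of admissions is not a difference between arms.

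It can also be said that an article may leave the operational query to the full protocol. That is fair for query detail. It does not excuse a criterion that is wrong as printed. Nor does it answer the timing point, which follows from the article's own choice to select controls after the intervention period.

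**Conclusion.** The point holds in two parts of unequal weight. First, the version label and the code range do not match. This is a definite error in the text, minor in itself, and it leaves the sampling frame not reproducible as printed. Second, acute codes, no required diagnosis date and a control draw after the intervention period together allow a control to qualify through an admission that is then counted as a primary outcome event. This is the part to act on.

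The size is at least one admission for each affected control, 0.0029 per control patient at 350 controls. The number affected is unknown. The mechanism assumes that controls are drawn on codes present at the time of the draw and that all admissions in the window are counted; the article states nothing to the contrary. Bias between arms is therefore a risk that the design leaves open, and it is not demonstrated.

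**What to change.** 1. In Participants, name the code system that the records actually use and give one code list in that system. Apply the identical list to the 15-center and the 72-center extraction.
2. Require the first IHD code to be dated before the start of follow-up in both arms. For controls, use the start of the same period already named under Blinding.
3. State in Outcome measures that the admission through which a patient qualified is not counted as an outcome event. With rule 2 in place this mainly covers an admission that spans the start date.

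The cost is a line or two of text and a date condition in the query, assuming that the records hold the date of first coding. A few recently diagnosed patients leave the frame. No added visits or measurements are needed.
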